#### Statistical techniques common to the analysis of primary and secondary outcomes

We will use multivariable fractional polynomials to test the linearity of the predictor-log risk association in the case of BRM/PRM and that of the predictor-score association in the case of RE-LRM (Royston and Sauerbrei 2008). In the case of missing data, provided that a missing at random (MAR) mechanism is justifiable, we will use multiple imputation for chained equations (MICE) to obtain plausible values of the missing variables from those available (White et al. 2011; van Buuren 2018). To this end, we will use at least 100 multiple imputation datasets. (Note that RE-LRM models are still reliable in the presence of MAR-type missingness.) The statistical analysis will be performed using Stata 18.5 (Stata Corporation, College Station, TX, USA) and R 4.4.1 (R Foundation for Statistical Computing, Vienna, Austria, EU).

## Discussion

FS is highly prevalent in the general population, with its incidence having risen dramatically in the past decade (Giorgi et al. 2023). The condition is primarily characterized by chronic, widespread pain and is often accompanied by additional symptoms such as anxiety, depression, sleep disturbances, and cognitive issues, all of which significantly affect the patients’ quality of life (Mease 2005; Sarzi-Puttini et al. 2020).

Effective management of FS requires a multidisciplinary and multimodal approach, combining pharmacological and non-pharmacological treatments (Macfarlane et al. 2016; Ariani et al. 2021). Non-pharmacological therapies are particularly recommended as the first line of treatment (Kundakci et al. 2022; Jurado-Priego et al. 2024). Among these, BT is recognized as a valuable complementary treatment, with numerous meta-analyses, systematic reviews, and randomized controlled trials supporting its efficacy, tolerability, and safety in FS management (Fioravanti et al. 2007, 2018; Naumann and Sadaghiani 2014; Cao et al. 2021; Maindet et al. 2021; Ducamp et al. 2022; Colas et al. 2024; García-López et al. 2024).

The goal of this study will be to assess the effects of BT on pain, function, quality of life, anxiety, and depression in a large cohort of patients with moderate to severe FS, through a prospective, multi-center observational study. We plan to enroll patients with primary FS who have FIQ score of 39 or higher and have had stable treatment for at least three months.

BT has been shown to provide significant benefits in managing FS, addressing both physical and psychological symptoms of the disease. Current scientific literature and our previous studies indicate that BT can lead to improvements in pain, physical function, quality of life, and anxious-depressive symptoms, with effects lasting beyond the immediate post-treatment period (Fioravanti et al. 2007, 2018; Paoloni et al. 2017; Maccarone et al. 2023). Therefore, we hypothesize significant improvements both immediately following treatment and one month after the treatment. The therapeutic effects of BT are multifaceted (Cheleschi et al. 2021). Hot stimuli have analgesic effects and reduce muscle tone; BT increases the secretion of β-endorphin, corticotrophin, cortisol, growth hormone, prolactin and influences the serotonin and dopamine function helping to improve the characteristic symptoms and quality of life of FS patients (Cheleschi et al. 2021; Gálvez et al. 2024; Antonelli et al. 2024a, b). BT treatments decrease circulating levels of Prostaglandin E2 (PGE2), Leukotriene B4 (LTB4) and Interleukin-1β (IL-1β), important mediators of inflammation and pain in this pathological condition (Ardiç et al. 2007). Finally, BT is able to reduce oxidative stress in patients suffering from FS (Çetinkaya et al. 2020).

Furthermore, combining BT with physical therapy or other standard treatments has been shown to produce superior outcomes compared to conventional therapies alone, especially in terms of long-term pain relief, respiratory function, and overall disability (Tognolo et al. 2022). Therefore, we also expect that the combination of BT with standard therapy (both pharmacological and non-pharmacological) will demonstrate superior outcomes compared to standard therapy alone.

BT also offers significant mental health benefits, particularly in reducing anxiety and depressive symptoms common in FS. Its anti-inflammatory effects may influence brain chemistry, as inflammation is linked to mood disorders like depression (Fioravanti et al. 2024, Koroglu and Yıldız 2024). Notably, IL-6, an inflammatory marker, is associated with sleep disturbances, and BT’s ability to regulate IL-6 could be a key mechanism behind its positive effects on sleep quality. In addition, warm, mineral-rich water promotes relaxation and reduces stress, contributing to better sleep patterns (Antonelli et al. 2024a, 2024b). This restorative sleep further enhances the benefits of BT by reducing fatigue and improving psychological resilience, ultimately leading to better overall well-being (Moini Jazani et al. 2023; Manica et al. 2024).

Furthermore, we expect to confirm a good tolerability of BT in a large sample of patients with moderate-severe FS.

In conclusion, the favorable effect of BT extended to several domains, including quality of life, anxiety and depression, could be particularly useful in the multimodal treatment of this disease.

A notable strength of this study is its large sample size and the involvement of nine specialized public facilities across Italy, which ensures a comprehensive representation of the national context.

Moreover, the results of this study have the potential to provide valuable insights that could help shape best practices for the clinical management of FS. Additionally, it may offer new evidence to further validate the role of BT as part of the complex approach to treating FS.

Nevertheless, there are some limitations to consider. Firstly, the observational nature of the study is a key limitation. Secondly, there will be no standardization of the BT treatments, as different mineral waters and specific protocols will be employed at each center, which is consistent with a real-world study design. Similarly, the routine care for FS, including both pharmacological and non-pharmacological treatments, will not be standardized but will follow the recommendations provided by the EULAR guidelines (Macfarlane et al. 2016).

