## Methods

### Study design and ethics

FIBROTHERM is a prospective multi-center, two-cohort observational study. The enrollment period will take place from April 2023 to November 2024 (deadline for the enrollment of the last patient) by the centers participating in the study. From June 2025, the data will be analyzed and then, disseminated. The estimated total duration of the study will be 26 months.

The study will be conducted in accordance with the “Declaration of Helsinki (1964) and following amendments. All eligible patients will provide a written informed consent, and this will be recorded in the appropriate outpatient file. The study protocol was approved by the Ethics Committee of the Area Vasta Sud Est-Toscana (Italy) on March 2023; the same document was submitted and approved by local Ethics Committees of the other participating centers to ensure that all local regulatory requirements were met. Furthermore, the study was registered on http://www.clinicaltrials.gov: NCT05801497.

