### Sample size

The primary outcome is the modification of the FIQ total score, whose minimum clinically relevant difference is 14% as compared to its initial value (Burckhardt et al. 1991). We expect a decrease in the FIQ total score of at least 14% in the 30% of the control cohort and 45% in the BT cohort. A number of 217 patients per group allows estimating an absolute difference of 15% (45—30%) in the incidence of the primary outcome between the two cohorts at an alpha level = 0.05 and with a power of 90% (Pearson’s chi-squared test). Assuming a loss to follow-up of 20%, 260 (217 + 43) patients will be enrolled per group, for a total of 520 patients.

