### Statistical analysis plan

#### Primary outcome

The primary outcome of the study will be the difference in the proportion of patients with reduction in FIQ-Total score > 14% in the BT vs. the control cohort. As described above, Pearson’s chi-square test will be used to evaluate the statistical significance of this difference, considered clinically relevant if ≥ 15%, at an alpha = 0.05 level and with a power of 90%. Subsequently, a binomial regression model (BRM) will be used to quantify the size of this difference and its precision (95% confidence interval) (Long and Freese 2006). The response variable of the BRM will be the proportion of subjects with a reduction in the FIQ-Total score > 14% at 15 days, and the predictor will be the cohort (discrete: 0 = control cohort; 1 = BT cohort). The effect size estimated by the BRM will be expressed both as absolute and relative risk change. Marginal estimates with 95% confidence intervals of the percentages of patients with reduction in FIQ-Total score > 14% in the two cohorts will be calculated.

In the BT cohort, we will also use a BRM having as a response variable, the proportion of subjects with a reduction in the FIQ-Total score > 14% and time as predictor (discrete; 0 = 15 days; 1 = 45 days) to verify the stability of the change in the FIQ-Total score at 30 days. A Bonferroni correction will be used to correct the 95% confidence intervals and associated p-values. The univariable BRM described above for the evaluation of the primary outcome between the BT and control cohorts will subsequently be expanded to a multivariable model by adding predictors (= potential confounders) determined preliminarily with the clinicians participating in the study. An univariable selection of the predictors will not be made, but they will be progressively added to the model to verify the effect on the relative risk estimated by the model itself (Greenland and Pearce 2015). Interactions initially determined or suggested by the multivariable analysis may also be included among the predictors. It is possible, and indeed expected, that the BRM will have to be replaced by a Poisson regression model (PRM) with robust confidence intervals, to overcome the well-known problems of fitting a BRM with multiple predictors (Zou 2004; Lumley et al. 2006). At this stage, we will only model the relative risk because, being this a cohort study, the relative risk measure is expected to be more transferable than the absolute risk.

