#### Secondary outcomes

The secondary outcomes of the study will be the differences in VAS, SF-12, STAI, and CES-D between the BT and control cohorts. These differences will be evaluated using a random effects linear regression model (RE-LRM) (Rabe-Hesketh and Skrondal 2021) 39. The response variable of such models will be the (continuous) score obtained from the scale and the predictors will be: 1) time (discrete; 0 = baseline; 1 = 15 days), 2) the cohort (discrete; 0 = control cohort and 1 = BT cohort), and 3) a time*cohort (discrete*discrete) interaction, with the random effect assigned to the patient. A Bonferroni correction will be used to correct the 95% confidence intervals and associated p-values. As already described for the BRM used for the evaluation of the primary outcome, also the RE-LRM will be expanded to a multivariable model by adding predictors (= potential confounders) determined preliminarily with the clinicians participating in the study. Interactions initially determined or suggested by the multivariable analysis may also be included among the predictors. An univariable selection of the predictors will not be carried out, but predictors will be progressively added to the model to verify the effect on the estimate of the difference in the scores for the BT and control cohort (Greenland and Pearce 2015).

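### The primary test and risk difference ignore centre, although cohort follows patients' acceptance of BT at nine centres and no rule balances the cohorts within centre

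*Protocol article*

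**What the plan says.** All places are in the protocol article.

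- **Cohorts.** Interventions and study arms describes two parallel cohorts. Controls are patients who decline BT. Settings of the enrollment lists nine centres across Italy, in rheumatology or rehabilitation units. The only enrolment target is 260 per cohort overall (Sample size). No ratio, quota or matching by centre is stated.
- **Heterogeneity.** The limitations in the Discussion say that "different mineral waters and specific protocols will be employed at each center". The next sentence says that routine care, too, is not standardised beyond following the EULAR recommendations.
- **Primary analysis.** A Pearson chi-square compares the cohorts, with 15 percentage points as the clinically relevant difference. A binomial regression then estimates the absolute and relative effect, and "the predictor will be the cohort (discrete: 0 = control cohort; 1 = BT cohort").
- **Secondary analyses.** The linear models contain time, cohort and their interaction, "with the random effect assigned to the patient".
- **Later adjustment.** Both models are afterwards extended, step by step, with confounders agreed with the clinicians. None is named. For the primary outcome this stage estimates the relative risk only.

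**The concern.** Without randomisation, each centre's mix of BT patients and controls is whatever local acceptance produces. If centres also differ in the proportion of patients who improve (case mix, routine care, how questionnaires are given), part of the BT-control contrast is a contrast between centres.

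This is separate from patients' own reasons for refusing. It would remain even if accepters and refusers within a centre were fully comparable. Unlike refusal bias, it can be removed with a variable the study necessarily holds. At stake are the declared significance test and the absolute difference by which clinical relevance will be judged.

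**Working it through.** **1. The plan's own figure.** Inputs from Sample size: responders "at least 14% in the 30% of the control cohort and 45% in the BT cohort"; "at an alpha level = 0.05 and with a power of 90" per cent; Pearson chi-square. Two-sided, without continuity correction, this gives 217 per group (power 90.0%), as stated. The figure assumes independent patients and no centre structure. With 260 enrolled and 20% lost, 260 × 0.80 = 208 per cohort remain (power 88.8%). I use 208 below.

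**2. Mechanism, by hand.** Assume no BT effect and two equal-sized groups of centres with responder rates of 45% and 25%. Let 60% of BT patients and 40% of controls come from the first group.
- BT: 0.6 × 45 + 0.4 × 25 = 37%
- Control: 0.4 × 45 + 0.6 × 25 = 33%
- Spurious difference: 4 points. At 217 per group the crude test rejects in 14% of studies instead of 5%.

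Here share and rate are fully aligned, so this shows the mechanism and is not a forecast.

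**3. Nine centres, no BT effect.** Assumptions, none of them in the documents: equal expected centre size, mean BT share 50%, mean responder rate 37.5% (midpoint of 30% and 45%), share SD σs, rate SD σr, correlation ρ.

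- Mean bias of the crude difference = (8/9) × ρ × σs × σr / (0.5 × 0.5)
- SD added by centres = σs × σr × √(1 + ρ²) × (√8/9) / 0.25
- Standard error assumed by the crude test = √(0.375 × 0.625 × 2/208) = 4.75 points, so it rejects beyond 1.96 × 4.75 = 9.30 points

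For σs = 20 and σr = 10 points:
- ρ = 0: added SD = 0.02 × 0.3143/0.25 = 2.51 points. Total SD = √(4.75² + 2.51²) = 5.37. Type I error = 2 × [1 − Φ(9.30/5.37)] = 8.3%.
- ρ = 0.5: bias = 0.889 × 0.01/0.25 = 3.6 points. Added SD = 2.81, total 5.52. Type I error = [1 − Φ((9.30 − 3.56)/5.52)] + Φ((−9.30 − 3.56)/5.52) = 15.9%.

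Simulation (416 patients, 6,000 studies per scenario) against the formula:

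| σs / σr (points) | ρ | Crude, formula | Crude, simulated | Mean bias, simulated | Centre-stratified CMH, simulated |
|---|---|---|---|---|---|
| 10 / 5 | 0 | 5.2% | 5.1% | about 0 | 5.0% |
| 10 / 5 | 0.5 | 5.7% | 5.4% | 0.8 points | 4.9% |
| 20 / 10 | 0 | 8.3% | 8.4% | about 0 | 5.2% |
| 20 / 10 | 0.5 | 15.9% | 15.2% | 3.5 points | 5.1% |

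Repeat simulations of the 20/10 scenarios gave 8 to 9% at ρ = 0, and 15 to 16% with bias of 3.5 to 3.7 points at ρ = 0.5.

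**4. Price of stratifying.** The share of information kept is about 1 − 4σs². At σs = 0.20 this is 0.84, so 0.84 × 208 ≈ 175 effective patients per cohort. For 30% against 45%, power is then about 83%, and simulation also gives 83%.

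**The case against.** The strongest reply is that adjustment is planned. The primary and secondary models are both extended with confounders chosen with the clinicians, centre is an obvious candidate, and an article may leave the list to the full plan. That stands as far as it goes: the absence of a covariate list is no fault here. It does not rescue the primary analysis, because the article itself fixes the significance test as crude and confines the adjusted stage to the relative risk. No choice of covariates at that stage changes the test or the absolute difference.

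Four stronger readings might be inferred, and the documents do not support them.

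- **That the cohorts are recruited at different places or times.** The article calls them parallel and gives both the same nine centres and one window ("The enrollment period will take place from April 2023 to November 2024"). What can be said is that no rule secures balance within centre.
- **That season confounds the result.** Season is mentioned nowhere, and nothing suggests that a 15-day change in FIQ depends on the month.
- **That the sentence on waters and protocols shows confounding by centre.** It describes variation in what BT patients receive, which touches no control. The remark on routine care is more relevant, but it does not say that care differs by centre.
- **That the 5% error rate is wrong.** This holds only if BT share and responder rate both vary appreciably between centres. At SDs of 10 and 5 points the crude test is close to nominal.

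**Conclusion.** The point holds conditionally. The declared primary test and the absolute risk difference take no account of centre, in a design where nothing balances cohorts within centre, and the planned later adjustment reaches neither. The harm requires variation between centres in both BT share and responder rate. Under assumed SDs of 20 and 10 points, type I error is 8 to 9% without correlation. At correlation 0.5 it is about 16%, with a bias of roughly 3.5 points against a planned effect of 15. Under SDs of 10 and 5 points there is practically nothing to correct. The documents do not show which case applies. A stratified test holds about 5% in every scenario tabulated, so the change is worth making before the data are analysed.

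**What to change.** - Make the primary test a Cochran-Mantel-Haenszel test stratified by centre, and the primary absolute effect a Mantel-Haenszel risk difference with its 95% confidence interval. Keep the crude chi-square as a supporting result.
- Name centre as a fixed, pre-specified term in the binomial or Poisson models and in the linear models. In the linear models the effect is the time-by-cohort interaction, so add centre-by-time as well: a centre main effect alone shifts levels and leaves the comparison of changes essentially untouched.
- Report BT and control counts for each centre. Calendar period of T0 may be added as a sensitivity term. No rule on enrolment order is needed.

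**Cost.** This is a change of wording, using a variable already known. Centres with only one cohort drop out of the stratified estimate. Power depends on imbalance: about 83% at a share SD of 20 points and about 75% at 30 points, against 88.8% for the crude test with 208 per cohort and no centre effects. Restoring 90% at SD 20 would take 217/0.84 ≈ 259 evaluable patients per cohort. The loss is large only where imbalance is large, which is also where the crude result is least reliable.

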## Data Availability

The data collected and analyzed for the current study will be available from the corresponding author on reasonable request.
